## Background

Traumatic injury is responsible for a large and increasing proportion of the world’s burden of disease and is the fourth leading cause of death globally [1]. Half of all trauma deaths are due to bleeding and most of these will occur within 6 h from injury [2]. Haemorrhagic shock following injury has been shown to induce a clotting dysfunction (i.e. coagulopathy) within minutes [3–5]. Such early trauma-induced coagulopathy (TIC) may exacerbate bleeding and is associated with higher mortality and morbidity [4, 6, 7]. Many more injured patients will go on to develop different types of coagulopathy at different times during the course of their treatment, either as a result of their body’s ongoing response to trauma or as a consequence of their clinical care. Coagulopathic, haemorrhaging trauma patients have increased blood transfusion requirements, increased mortality and more adverse outcomes [8]. Despite improvements in surgical techniques, resuscitation strategies and intensive care treatments, outcomes for critically injured patients remain poor [9]. Within the last decade research focussing on TIC has led to improved resuscitation strategies, resulting in the early and more aggressive use of blood products and coagulation factors for the management of massively bleeding patients.

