Although considered a preventable major cause of death, the management of coagulopathic bleeding in trauma patients remains primarily based upon retrospective registry studies of survival and extrapolating the results of transfusion practice performed in the elective, non-acute surgical setting. Treatment is diverse comprising the empiric transfusion of red blood cells (RBC) and clotting product supplements to patients, blind to the type and severity of TIC they may have – or indeed even if they do not have coagulopathy. It is well established that blood transfusion carries significant health risks both related to transmission of pathogens and to the development of transfusion reactions. Published in 2015, the results of the Pragmatic, Randomised Optimal Platelet and Plasma Ratios (PROPPR) trial [19] provide the best evidence to date for optimal trauma haemorrhage resuscitation. PROPPR demonstrated that an empiric massive transfusion protocol (MTP) aiming at a ratio of 1:1:1 of blood components (RBC 1: plasma 1: platelets 1) administered from the early phase of care and during ongoing haemorrhage was associated with fewer exsanguinations in the initial 24 h (*p* = 0.03) and a tendency towards improved 24-h survival (*p* = 0.12) than a 1:1:2 ratio.

The present prospective randomised controlled trial (RCT) will employ evidence-based treatment algorithms to compare outcomes of VHA-guided resuscitation versus CCT resuscitation support in haemorrhaging trauma patients.

The hypothesis for this comparative study is that VHA-directed therapy will enhance early haemostatic control by the targeted correction of TIC, whilst also reducing the total amount of blood products and procoagulants administered to all bleeding trauma patients, including those not having TIC. This would significantly reduce both the number of patients receiving blood transfusion and the number of transfused blood products per transfused patient, thereby improving both patient safety and resource utilisation.

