### Secondary endpoints

The secondary endpoints listed below will be analysed in order to provide a sensitive and comprehensive description of outcomes and health care resource demands for the VHA and CCT arm subjects:All-cause mortality at 6 and 24 h and 28 and 90 days post admissionDuration and severity of coagulopathy until haemostasis, as defined by the area under the time multiplied by Prothrombin Ratio (PTr) curve, with coagulopathy defined as PTr > 1.2. Patients who die will have their time of haemostasis set at 24 h, and last PTr extrapolated to this time pointProportion of patients who have corrected coagulopathy, defined as PTr < 1.2, after first 8 units of RBCTime to haemostasis (defined as having occurred at the end of the first hour free of red cell transfusions and the treating clinicians believe primary haemostasis has been achieved)Time spent in coagulopathic condition, defined as PTr ≥ 1.2, until haemostasis, defined as the point 1 h from the last administration of RBC and the treating clinician believes that primary haemostasis has been achievedBlood products administered (RBC, plasma, platelets alone and in total) within first 6 and 24 h after admission28-day ventilator-free and ICU-free days (patients who die in hospital during the 28-day study period will be considered to have zero hospital-free days)Total hospital length of stay28-day symptomatic thromboembolic events defined as: deep venous thrombosis (DVT) diagnosed by compression ultrasound or venography, pulmonary embolism diagnosed by computed tomography (CT) pulmonary angiogram or ventilation-perfusion scan or myocardial infarction and/or stroke identified by standard clinical diagnostic investigation(s)Incidence of transfusion-related complicationsIncidence of organ dysfunction, defined by Sequential Organ Failure Assessment (SOFA) scoreHealth care resource, productivity costs and HRQoL (EuroQol EQ-5DTM at discharge or day 28, and at day 90)Lifetime health economic cost-effectiveness of personalised VHA-guided haemorrhagic treatment versus MTP-based on best practice and CCTs

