#### Ventilator-free days

Calculated by the subtracting the number of days spent on mechanical ventilation from 28. Death before day 28, recorded as 28.

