#### Length of stay

Length of stay will be recorded in days, for the total number spent in ICU and in hospital. If the patient is in the hospital at any time point during a day, this day will be considered a hospital day.

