#### Method of analysis

All primary and secondary outcomes will be analysed as intention-to-treat, and will include all randomised patients for whom the primary outcome of ‘alive’ and ‘free of massive transfusion’ at 24 h is recorded. The primary endpoint of patients who are alive and free of massive transfusion at 24 h will be assessed by difference in proportion with 95% confidence intervals. The chi-square test or Fischer’s exact test will be used were appropriate. Absolute risk reduction and relative risk reduction by VHA-guided therapy will be calculated.

Kaplan-Meier mortality estimates between the two arms for all-cause mortality at 6 and 24 h, as well as 28 and 90 days post admission, will be estimated for the secondary endpoint of death.

A per-protocol analysis and a sensitivity analysis will be performed for the primary endpoint. The following patients will be excluded from the per-protocol analysis:Patients who do not have at least one ROTEM®/TEG®/CCT test performed *and*
Who die within 60 min after baseline blood sampling *or*
Who achieve haemostasis within 60 min of baseline sampling

Both ROTEM®-guided and TEG®-guided therapy together (i.e. the VHA arm) will be compared with the CCT arm. Separate analyses will be performed for ROTEM®-guided and TEG®-guided therapy alone for primary endpoints and correction of coagulopathy.

All applied tests will be two-sided and *p* values of 0.05 will be accepted as statistically significant. We will report *p* values with and without correction for multiple testing.

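### Total hospital length of stay is compared between arms with no rule for death, so early deaths count as short stays; the only hospital-related death rule belongs to an endpoint that is not listed

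*Protocol article*

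**What the plan says.** Hospital stay is a stated aim in the Secondary objective section and appears in Secondary endpoints as "Total hospital length of stay". The Length of stay section gives the counting rule: "If the patient is in the hospital at any time point during a day, this day will be considered a hospital day". Neither place gives a value for a patient who dies.

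Secondary endpoints does contain a hospital-related death rule, in brackets after the ventilator-free and ICU-free days item: "patients who die in hospital during the 28-day study period will be considered to have zero hospital-free days". No hospital-free-days endpoint is listed there or elsewhere in the article. The same list fixes a death rule for the coagulopathy area under the curve, setting haemostasis at 24 h and carrying the last prothrombin ratio forward.

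Method of analysis keeps deaths in: "All primary and secondary outcomes will be analysed as intention-to-treat, and will include all randomised patients for whom the primary outcome" is recorded. The Sensitivity analyses section deals with missing data only, and a stay ended by death is not missing. On timing, the Background says: "Half of all trauma deaths are due to bleeding and most of these will occur within 6 h from injury".

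**The concern.** A shorter stay is normally read as a better result. In this population a very short stay can mean rapid recovery or death soon after arrival, and raw length of stay does not separate the two. If VHA guidance saves lives, patients who would have contributed one day contribute a full admission instead, and the comparison of stay moves against VHA. If VHA guidance costs lives, the comparison moves in its favour.

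This is more than a gap that a later document might fill. The article supplies a death rule and attaches it to a measure it does not list, while the hospital endpoint it does list has none.

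**Working it through.** **Plan's own figures.** The article gives no expected stay, no mortality rate and no product means, so there is no figure of its own to reproduce. Its sample size (28% vs 15% for massive transfusion or death, 196 per arm) concerns the primary endpoint and does not change the argument.

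**Hospital stay.** Let *d* be the proportion dying early, *L* the mean stay of survivors (the same in both arms) and 1 day the stay of a patient who dies on the day of admission (Length of stay section). Then

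mean stay = (1 − *d*) × *L* + *d* × 1,

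and the difference between arms is −(*d*₁ − *d*₀) × (*L* − 1). Only the mortality gap and *L* matter. Both are assumed here.

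| Survivor mean *L* (days) | Mean at 15% deaths | Mean at 20% deaths | Difference | Mean at 25% deaths | Difference |
|---|---|---|---|---|---|
| 15 | 12.90 | 12.20 | −0.70 | 11.50 | −1.40 |
| 20 | 17.15 | 16.20 | −0.95 | 15.25 | −1.90 |
| 30 | 25.65 | 24.20 | −1.45 | 22.75 | −2.90 |

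For example, with *L* = 20: 0.85 × 20 + 0.15 × 1 = 17.15 and 0.80 × 20 + 0.20 × 1 = 16.20. Survivors are identical, yet the arm with more deaths shows the shorter stay in every row. If those who die stay *s* days on average, 1 is replaced by *s*, and the sign holds as long as *s* is below *L*.

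**Plausibility of the gap.** The planned difference in the whole primary composite is 28 − 15 = 13 points, so a 10-point gap in early mortality alone is a generous upper value.

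**Size against noise.** Assume a lognormal stay with median 18 and mean 25 days. Its SD is 25 × √((25/18)² − 1) ≈ 24 days, and the standard error of a difference at 196 per arm is 24 × √(2/196) ≈ 2.4 days. With *L* = 25 the artefact is 0.05 × 24 = 1.2 to 0.10 × 24 = 2.4 days, about half to one standard error.

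**Effect of scoring death as zero hospital-free days.** Suppose every survivor stays exactly 20 days, giving 28 − 20 = 8 hospital-free days. The means are 0.85 × 8 = 6.8 at 15% deaths and 0.80 × 8 = 6.4 at 20%. The arm with more deaths now looks worse by 0.4 days.

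**Blood products at 24 h.** Assume survivors average 8 RBC units and those who die average *k*. The arm with more deaths differs by (*d*₁ − *d*₀) × (*k* − 8).

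| *k* (units) | 15% vs 20% | 15% vs 25% |
|---|---|---|
| 4 | −0.2 | −0.4 |
| 8 | 0 | 0 |
| 14 | +0.3 | +0.6 |

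The sign depends on *k*, which the article does not give.

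**The case against.** - *The article is condensed.* It refers to a full protocol in Additional file 1, and neither that nor an analysis plan is at hand; Method of analysis names no test for stay. Silence alone would be no finding. What stands against the article is the mismatch between the rule it prints and the endpoint it lists.
- *The bracket may be a slip for ventilator-free or ICU-free days.* It may well be. In that case length of stay has no death rule at all, and the bracket still needs correcting. It also needs reconciling with the Ventilator-free days section, which says "Death before day 28, recorded as 28"; that is a separate point.
- *Stay is a resource measure.* Beds actually used are a valid quantity for cost-effectiveness, and raw stay should be kept for that. It is still a poor basis for saying which arm did better.
- *Harm would be visible anyway.* All-cause mortality is reported at 6 h, 24 h, 28 days and 90 days, and the primary endpoint counts death as failure. This limits the risk of misreading but does not make the stay comparison interpretable.
- *The artefact is small against noise.* On the assumed spread it is at most about one standard error. It is nevertheless systematic, and a larger sample would not remove it.

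A reader might also infer that the product totals favour the arm with more early deaths, since patients who die stop receiving products and the hypothesis includes "reducing the total amount of blood products and procoagulants administered to all bleeding trauma patients". The documents do not support that. Death does cut a patient's own count short, but patients who bleed to death may already have received more units than survivors receive in total, and an arm with more bleeding deaths may also have bled more.

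**Conclusion.** The point holds for hospital stay. As written, the endpoint rewards early death, and the only hospital-related death rule governs a measure that is not listed. The direction is fixed provided survivors' stays are similar between arms and those who die have shorter stays than survivors. The size, about 0.7 to 2.9 days in favour of the arm with more deaths, rests wholly on assumed survivor means of 15 to 30 days, mortality gaps of 5 to 10 points and deaths on the day of admission.

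For the 6 h and 24 h product totals, the documents support only that they are truncated by death. The net effect could go either way (−0.4 to +0.6 units on the assumed values), so no claim of bias towards one arm is justified. Nor is a test that ranks deaths worst on product use: it would turn a resource measure into a mortality composite that largely repeats the primary endpoint.

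**What to change.** 1. In Secondary endpoints, list 28-day hospital-free days, with in-hospital death scored zero, as the comparative hospital-stay endpoint. The bracketed rule then has an endpoint to govern.
2. Keep total length of stay under the existing day-counting rule as a descriptive measure and as an input to the cost-effectiveness model.
3. Show mortality and raw stay beside hospital-free days.
4. Report the 6 h and 24 h product totals together with mortality at the same time points. No change of test is needed.

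The cost is a change of wording and one derived variable. All the data are already collected and no sample-size figure changes. The downside is that hospital-free days combine death with stay, and a survivor still in hospital at day 28 also scores zero; item 3 is there so that readers can separate the two.

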### Study procedures

#### Screening procedures

Local investigators will identify eligible adult trauma patients with haemorrhagic shock and ongoing bleeding as soon as possible after the patient has arrived in the emergency department (ED), using local transfusion triggers. If patients are deemed to be eligible, consent for entry into the trial will be sought. A screening log will be completed once a week, which will record all patients considered for eligibility to the trial by the investigator(s). The log will include age, gender, inclusion/exclusion criteria and other reasons for non-enrolment. The screening log data will be reviewed at regular intervals.

#### Randomisation procedure

Enrolled patients will be block randomised per centre to either the CCT or the VHA study arm within 3 h of injury and within 1 h of admission. The trial will be un-blinded for clinical staff and site investigators. Once a patient is determined eligible for the study and informed consent or agreement has been obtained, each subject will be enrolled as soon as possible and will be assigned a unique alphanumeric study identifier. Randomisation will be performed by the site investigator opening a sealed envelope containing the randomised treatment group, to allow for immediate allocation of subjects. An independent party, appointed by the sponsor, will generate the randomisation sequence and site envelopes centrally.

#### Schedule of intervention

All participating centres will initiate the management of the study population according to standard local protocols regardless of enrolment in the trial. Following randomisation, study participants will undergo interventions at set time points as outlined in Fig. 1 (Standard Protocol Items: Recommendations for Interventional Trials (SPIRIT) schedule of enrolment, interventions and assessments) and be followed up for 90 days after enrolment.

### Standard care

All participating centres currently manage critically bleeding trauma patients according to a standardised MTP aiming at a ratio of RBC 1: plasma 1: platelets 1 (1:1:1), typically administering plasma from the start of resuscitation and platelets immediately as they become available. Tranexamic acid (TXA) will be administered to all patients as an intravenous bolus of 1 g over 10 min (either pre-hospital or in the ED) followed by an intravenous infusion of 1 g over 8 h, providing that the patient is less than 3 h post injury.

Current use of additional diagnostics and therapy, such as systematic approach according to Advanced Trauma Life Support (ATLS®) principles, early imaging (e.g. X-rays, Focussed Assessment with Sonography for Trauma (FAST), computer tomography (CT)), activation criteria for MTP, surgical approach applying damage control principles when indicated, the availability and use of interventional radiology, will not be affected in either of the study groups. An optimised initial MTP based on a 1:1:1 balanced transfusion will be implemented in all centres for approximately 2 months prior to initiation of the RCT and standardised as far as local routines and blood product availability allow.

### Initiation of study care

Corresponding and optimised algorithms based on VHA trigger parameters for the VHA arm and CCT results for the CCT arm, respectively, have been developed and will be applied in the enrolled subjects (Fig. 3a, b, c). During active haemorrhage, samples will be taken for CCT/VHA analysis at baseline and after every 4 units of RBC until haemostasis. The results from each blood sample will be acted upon as soon as they are available. For the VHA arm, this implies acting upon the parameters as they are appearing, not waiting until the VHA trace is completed.

**Fig. 3 Fig3:**
[figure not shown]
Algorithms

If a planned study intervention has not yet been administered, the sample will be taken and analysed (where resources allow) but will not be used to guide study intervention. The first sample taken after a study intervention is actually administered will be the next sample used to guide study intervention based upon the respective protocol.

The same blood products and procoagulants will be employed in both study arms, with existing standard practice in all participating centres being closely aligned to that of the CCT arm. Trial products will be given as an addition to the 1:1:1 baseline MTP and TXA. The procoagulants included in the algorithms are fibrinogen concentrate or cryoprecipitate and additional platelets, plasma and TXA.

Enrolled patients will be block randomised per centre to either study arm:CCT: haemostatic resuscitation (standard care), based on a MTP aiming at ratio 1:1:1 of blood components (RBC 1: plasma 1: platelets 1) and TXA, and CCTs to guide further resuscitation with blood products and procoagulant factorsVHA: haemostatic resuscitation (standard care), based on a MTP aiming at ratio 1:1:1 of blood components (RBC 1: plasma 1: platelets 1) and TXA, and VHA-guiding further resuscitation with blood products and procoagulant factors

### Randomised study care – VHA arm

VHA will be conducted for all subjects in the VHA arm at each time point up to 24 h. During active haemorrhage, samples will be taken for VHA analysis at baseline and after every 4 units of RBC until haemostasis. The clinical course of subjects randomised to the VHA arm will follow a treatment algorithm utilizing VHA results (Fig. 3a and b). The subject will be treated with standard haemostatic resuscitation based on a MTP aiming for 1:1:1 ratio of blood components and initial TXA. In addition, according to threshold values in the algorithms, the subjects will be given fibrinogen concentrate or cryoprecipitate and/or additional platelets, plasma and TXA depending on the VHA results.

Fibrinogen concentrate or cryoprecipitate will be administrated when FIBTEM Clot Amplitude at 5 min (CA5) is below 10 mm or functional fibrinogen (FF) TEG® Maximum Amplitude (MA) is below 20 mm. Additional platelets are indicated when the subtracted amplitude of FIBTEM CA5 from EXTEM CA5 is below 30 mm, or the subtracted amplitude of FF TEG® MA from rapid TEG® MA is below 45 mm. Additional plasma is indicated when the results show a normal EXTEM CA5, defined as above 40 mm, but still a prolonged EXTEM clotting time (CT), defined as above 80 s, or normal rapid TEG® MA, defined as above 65 mm, but still a prolonged rapid TEG® activated clotting time (ACT), defined as above 120 s. Additional TXA is indicated when the EXTEM Lysis Index at 30 min (LI30) is below 85% or rapid TEG® clot lysis at 30 min (Ly30) is above 10%.

This VHA treatment algorithm is based upon analysis of more than 2200 trauma subjects enrolled to a prospective observational study conducted at the participating study sites, entitled Activation of Coagulation and Inflammation in Trauma (ACIT). Analysis of the ACIT dataset has enabled the definition of clinically relevant VHA thresholds and patterns by which it is possible to rapidly identify coagulopathic patients and anticipate the need for massive transfusion. These threshold parameters have been applied to the generation of an evidence-based targeted treatment algorithm.

According to pre-designation, each study centre will only conduct VHA using either thromboelastography (TEG®) or rotational thromboelastometry (ROTEM®) to determine the following parameters:TEG®: RapidTEG® ACT, MA and Ly30; functional fibrinogen TEG® MAROTEM®: EXTEM CT, CA5 and Li30; FIBTEM CA5

### Randomised study care – CCT arm

CCTs will be conducted for all subjects in the CCT arm at each time point up to 24 h. The tests will comprise platelet counts (PLT), activated partial thromboplastin time (aPTT), prothrombin time – international normalised ratio (PT/INR) and Clauss fibrinogen assay. PTr and Clauss fibrinogen will be measured for all study subjects at each time point.

The clinical course of subjects randomised to the CCT arm will follow a treatment algorithm utilizing CCT results (Fig. 3c) and based upon current published evidence and empiric best practice according to the PROPPR and CRASH-2 trials data (i.e. a 1:1:1 product ratio, with the anti-fibrinolytic TXA) [19–21]. The subject will be treated with standard haemostatic resuscitation based on a MTP aiming for a 1:1:1 ratio of blood components and initial TXA. In addition, the subjects will be given fibrinogen concentrate or cryoprecipitate and/or additional platelets and plasma depending on the CCT results.

Fibrinogen concentrate or cryoprecipitate will be indicated when fibrinogen values are below 2.0 g/L. Additional platelets will be indicated with PLT below 100 × 10^9^/L and additional plasma will be administrated when the INR is above 1.2 despite normal fibrinogen, defined as 2.0 g/L or above. There are no generally accepted indications for additional anti-fibrinolytic therapy using CCTs.

